## Abstract

**Background:**

Depression and anxiety disorders are increasing among the general population in the Western world. Individuals may need several kinds of treatment in order to maintain health, such as cognitive behavioural therapy (CBT) and drug treatment. However, having an everyday life that “works” is also important, suggesting a need for interventions based on activities that facilitate a satisfying everyday life. There is still lack of such evidence-based interventions. The Tree Theme Method^®^ (TTM) is an occupational therapy intervention designed for a client-centred context in which an individual develops strategies to become an actor in his or her everyday life. Previous studies of the TTM have focused on process evaluation; therefore, further studies are needed to evaluate the method’s effects. The aim of this paper is to outline an intervention that can evaluate the effects of the TTM in terms of psychological symptoms, as well as everyday occupations and well-being, in patients suffering from depression and anxiety.

**Methods/Design:**

This randomized clinical trial includes patients from three Swedish counties randomized to either intervention or treatment as usual. Men and women aged 18–65 years who have been diagnosed with either depression or anxiety are eligible for inclusion. Data collection is carried out at baseline, and outcomes are assessed at the end of intervention, as well as at 3 months and 12 months after intervention ends. The outcomes measured are psychological symptoms, everyday activities, and health-related factors.

**Discussion:**

Depression and anxiety may create difficulties for individuals in the activities of their everyday lives to the extent that they require diagnosis and intervention. Despite this reality, evidence-based interventions that focus on everyday activities are lacking. Therefore, it would be useful to design a specific method for occupational therapy intervention that does precisely that. This study provides insight into the effects of the TTM, comparing it to occupational therapy treatment as usual.

**Trial registration:**

ClinicalTrials.gov: NCT01980381; registered November 2013.

## Background

Depression and anxiety disorders are two major diseases, and their prevalence is increasing among the general population in the Western world. In Sweden, about 15 % of men and 25 % of women are affected at some point in life to such an extent that they need treatment [1]. When an individual suffers from depression or anxiety disorders, his or her ability to cope with various activities in everyday life [2, 3] and to relate to others may be limited, while experiencing various psychological symptoms and possible side effects from drugs. The problems related to the individual’s disease also contribute to high sickness rates. In 2011, depression and anxiety disorders each accounted for 12 % of the sicknesses in Sweden [4].

**Fig. 1 Fig1:**
[figure not shown]
Overview of study procedure

The Swedish National Board of Health and Welfare [1] recommends psychological approaches, such as cognitive behavioural therapy (CBT) and drug treatment, for patients diagnosed with depression or anxiety. But the Swedish National Board of Health and Welfare also suggests other interventions that are adapted to the individual’s needs, and the board has stated that having a satisfying everyday life at home and at work or school, along with a sense of belonging in a social context, is just as important as obtaining a proper diagnosis and appropriate psychological or pharmacological treatment [1]. We have not found any evidence-based treatment interventions that focus on everyday life, such as activities in connection with self-care, productivity (at home, at work, of at school), leisure, or relationships to others.

The Tree Theme Method^®^ (TTM) is an intervention that can complement CBT and pharmacological treatment. The TTM is designed for a client-centred clinical occupational therapy context [5] in which the patient paints pictures of trees that represent certain periods in his or her life. These paintings are used as a starting point for the patient to tell his or her life story, focusing on the mix of activities and routines in everyday life [6]. The intervention is based on knowledge about art therapy [7], life storytelling [8, 9] and the value of meaningful activities [10] in maintaining good health. The TTM intervention involves five sessions and is carried out during a defined period of 6–9 weeks. The approach aims to increase the individual’s ability to cope with everyday life [5], and its intention is to develop strategies for becoming active, thus enhancing patients’ satisfaction with the mix of activities and routines that compose their everyday lives [5].

The TTM has been evaluated in terms of processes. The first study to describe the method presented the case of a woman diagnosed with depression and anxiety who, after taking part in the intervention, became an actor in her own life – that is, she went from being unable to care for her family or manage her work to being active and effective in her everyday routine [5]. In an additional study [11], the TTM was evaluated in a group of patients (6 men and 29 women) diagnosed with depression or anxiety disorders, this time examining changes in their perceptions of health and activity after completing the intervention. The results showed consistently positive outcomes for the patient group regarding psychological symptoms, well-being, activity performance, therapeutic alliance, and patient satisfaction with the intervention. Further, better outcomes and higher client satisfaction correlated with higher ratings of the therapeutic alliance [11]. The TTM has also been evaluated in qualitative studies focusing on patients’ and therapists’ experiences of the method, including the therapeutic alliance [12, 13]. Overall, patients reported feeling that the TTM suggested that they could become focused and expressive, and that this in turn meant that they could change their everyday lives. They argued that the TTM marked a turning point at which they gained new perspectives on self-care, productivity, leisure, and their relationships with others [13]. The therapists experienced the TTM as a structured method for intervention, and they were impressed with the fact that the method could initiate a process of significant change for patients in such a short time (i.e., five sessions) [12]. A 3-year follow-up [14] used the same outcome measures presented in Gunnarsson and Eklund [16] – psychological symptoms, well-being, and activity performance – and demonstrated sustainable positive outcomes, particularly regarding increased ability to perform everyday activities both at home and at work.

It is important to offer patients with depression and anxiety disorders various interventions other than CBT and drug treatment alone, such as therapy that aims to enhance their satisfaction their everyday routines, as the TTM does. The focus of previous studies examining the TTM has been process evaluation, and therefore further studies should evaluate this intervention’s effects.

## Objectives

This paper outlines an occupational therapy intervention in order to evaluate the effects of the TTM. The primary objective concerns the psychological symptoms of depression and anxiety in diagnosed patients, as well as patients’ perceptions of their own performance of everyday activities and their satisfaction with that performance. The secondary objective is to evaluate various health-related factors, intervention-related aspects, and health-care consumption. We compare the outcomes for participants in the intervention group (TTM) with those in the control group (treatment as usual = occupational therapy as usual) in order to identify and explore the effects of TTM.

## Methods

### Study design

The study is a randomized controlled clinical trial (RCT) [15] of nonpharmacological treatment according to CONSORT recommendations [16]. Participants are randomized to either an intervention group or a control group. The study design is shown graphically in Fig. 1.

### Participants

Our study sample includes men and women between 18 and 65 years old who have been diagnosed by a physician with depression and/or anxiety and have been assessed as encountering difficulties in their everyday activities. We exclude patients with severe somatic disease or psychosis, as well as those with language difficulties or cognitive disorders that would impede their understanding of the self-rating questionnaires.

### Context and procedure

This study is being conducted at primary health-care centres and general outpatient mental-health-care units in three counties in the south of Sweden. Thirteen occupational therapists specifically trained in the TTM intervention ask patients who meet the inclusion criteria to participate and obtain informed consent from those who agree. In order to assess the therapeutic alliance, the occupational therapist does not meet a patient more than twice before asking him or her to participate in the study. Patients who do not wish to participate in the study receive the usual treatment. After recruiting, each patient is allocated to either the TTM or the control group (occupational therapy as usual). Drug treatment continues as prescribed, and dropouts are documented during the study. The same occupational therapists perform both TTM intervention and treatment as usual. In order to ensure that the occupational therapists actually deliver two different treatments they complete fidelity forms after each session.

### Intervention

#### The TTM intervention

Participants who are randomized to the TTM complete five sessions of 60 min each during a period of 6–9 weeks. In the TTM, each of the first four sessions starts with a progressive relaxation in which a specific theme is introduced, and the patient paints a symbolic tree. This picture is then used as a starting point for patients to tell their life stories, focusing on everyday activities. This part of the intervention constitutes a reflective dialogue between the patient and the occupational therapist aimed at identifying necessary changes in the patient’s life. The theme of the tree differs from one session to the next, and each tree represents a particular period of life: the present, childhood, adolescence, adulthood. In the fifth session, the focus is on story making and on shaping plans for the future. Patient and therapist also decide on tasks, linked to the patient’s identified difficulties and needs, that the patient completes between sessions.

#### Treatment as usual

Participants who are randomized to the control group complete five sessions of 60 min each during a period of 6–9 weeks. Each occupational therapist has defined what is meant by *occupational therapy as usual*. The focus of these sessions is dialogue, sometimes in combination with activities, regarding the patient’s well-being and his or her current activities in everyday life. Patients may or may not be assigned tasks between sessions.

### Training occupational therapists in the TTM

The occupational therapists that participated in this intervention study completed 50 h of standard training in the frames and techniques of the TTM provided by the Swedish Association of Occupational Therapists involving theory about client-centred occupational therapy, art therapy, and occupational storytelling and story-making with a focus on everyday activities. The training also involved practical exercises, including painting the different tree themes, in which the therapists work in role playing pairs, switching between client and therapist. In addition, the occupational therapists in this study also completed two additional days of training the study’s objectives and implementation.

### Data collection

Data collection for this study is being carried out by project assistants on four occasions: 1 to 2 weeks before intervention, immediately after intervention, 3 months after completion, and 12 months after completion. Sociodemographic variables—namely, gender, age, diagnosis, accommodation, social networks, level of education, and employment—are documented. In addition, physical activity and health-care consumption (number of visits to service providers in the preceding month), inpatient care, pharmacological treatment (for insomnia, depression, or anxiety), and pharmacological-treatment compliance are recorded, along with any other health-care consumption. The data collection is blinded, i.e. the project assistants are unaware of treatment assignment.

### Primary outcomes

*Psychological symptoms* are measured with the Symptom Checklist-90-R (SCL-90-R) [17]. This self-rating questionnaire measures psychological problems; it consists of 90 items rated on a five-step categorical Likert scale from zero to four, with higher scores indicating greater severity. In this study, the Global Symptom Index (GSI) of SCL-90-R is calculated. The SCL-90-R is used frequently and has been found to be reliable and valid [17, 18].

*Depression* is measured with the Montgomery-Åsberg Depression Rating Scale (MADRS-S) [19]. The self-rating questionnaire consists of nine items, each rated on a seven-step Likert scale from zero to six, with higher scores indicating greater severity. The MADRS-S is a commonly used measurement in clinical practice; it has been shown to have good internal consistency [20] and to be a useful screening instrument for depression [21].

*Anxiety and depression* are measured with the Hospital Anxiety and Depression Scale (HADS) [22]. The self-rating questionnaire comprises 14 items, and two subscales measure anxiety (7 items) and depressive symptoms (7 items), each rated on a four-step categorical Likert scale from zero to three, where higher scores indicate greater severity. The HADS is commonly used in clinical practice and has performed well in assessing symptoms of depression and anxiety disorders in a general population [22, 23].

*Everyday activities* are measured from three aspects: performance of and satisfaction with the performance of activities, satisfaction with everyday activities, and balance in everyday activities. *Performance of and satisfaction with the performance of activities* are measured with the Canadian Occupational Performance Measurement (COPM) [24], a semi-structured instrument focusing on self-care, productivity, and leisure. The patient identifies problematic tasks and activities and then rates his or her actual performance and satisfaction with that performance. The ratings apply a ten-step numeric Likert scale from 1 (not important at all) to 10 (extremely important). The patient then rates his or her performance and satisfaction with the performance of targeted tasks. The Swedish version used here has demonstrated high responsiveness to change [25] and clinical utility [26].

*Satisfaction with everyday activities* is measured with the tool Satisfaction with Daily Occupations (SDO) [9], a semi-structured interview focusing on perceived satisfaction with everyday activities in work, leisure, domestic tasks, and self-care. The individual first indicates whether he or she presently performs an activity and then rates his or her satisfaction with that performance on a seven-step numeric Likert scale from 1 (worst possible) to 7 (best possible). The original version has nine items and has demonstrated satisfactory internal consistency, construct validity [27, 28], and test-retest reliability [28]. The present study used a 14-item version in order to cover more activities in the areas of leisure, domestic tasks, and self-care; this version has also shown satisfactory internal consistency [29].

*Balance in everyday life activities* is measured with the Occupational Balance Questionnaire (OBQ) [30], a 13-item self-rating questionnaire that indicates an individual’s perception of balance. Balance is rated on a six-step categorical Likert scale, from 0 (completely disagree) to 5 (completely agree). The OBQ has shown good internal consistency and test-retest reliability [30].

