### Sample size/power calculation and randomization

The power calculation indicates that 60 patients would be needed in each group to obtain an effect size of 3.6 (scale on 9–63) for the outcome variable Satisfaction with Daily Occupations (SDO), with 80 % power (*p* = 0.05). To compensate for possible losses, a total of 130 patients will be recruited. After granting informed consent, patients are allocated (by means of sealed envelopes prepared by a researcher not involved in the study) to either intervention or treatment as usual. In all, 65 patients will be randomized to the TTM (intervention group) and 65 to treatment as usual (control group).

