### Statistical analysis

At the study’s completion, data analysis will be performed on the principle of intention to treat [15]; in other words, outcomes will be analysed using the basis of all participants. Missing data for dropouts will be estimated using the last data obtained before a participant dropped out. Descriptive and analytic statistics will be used to compare the outcomes between the intervention group and the control group at baseline, after intervention, and at 3- and 12-month follow-ups. As all variables will be assessed on either a nominal or an ordinal scale, statistical analysis with non-parametric methods will be used.

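### Six instruments (up to eight scores) are unranked primary outcomes compared at three follow-up times with none leading, while the sample size rests on SDO alone at an undivided 0.05

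*Protocol article*

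**What the plan says.** The Primary outcomes section of the protocol article covers six instruments.

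- SCL-90-R: "In this study, the Global Symptom Index (GSI) of SCL-90-R is calculated".
- Depression "is measured with the Montgomery-Åsberg Depression Rating Scale (MADRS-S").
- HADS: "two subscales measure anxiety (7 items) and depressive symptoms (7 items").
- Everyday activities "are measured from three aspects: performance of and satisfaction with the performance of activities, satisfaction with everyday activities, and balance in everyday activities". These are COPM, SDO and the Occupational Balance Questionnaire (OBQ) respectively. COPM yields two ratings: "The patient then rates his or her performance and satisfaction with the performance of targeted tasks".

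Secondary outcomes have their own heading, so the primary label looks deliberate. Nothing ranks the six.

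Under Statistical analysis, descriptive and analytic statistics will "compare the outcomes between the intervention group and the control group at baseline, after intervention, and at 3- and 12-month follow-ups". No time is given precedence.

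Under Sample size, 60 patients per group give 80% power at p = 0.05 to detect a difference of 3.6 on a 9–63 scale "for the outcome variable Satisfaction with Daily Occupations (SDO"). Neither the time point nor the standard deviation is given. The plan is to recruit 130 patients, 65 per group.

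Under Objectives: "The primary objective concerns the psychological symptoms of depression and anxiety in diagnosed patients". The sentence goes on to activity performance and satisfaction with it. It does not single out SDO and does not mention occupational balance, although OBQ is on the primary list.

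**The concern.** Three parts of the plan that should agree do not. The primary objective leads with symptoms, the primary-outcome list gives equal standing to symptoms and three kinds of activity measure, and the sample size treats SDO as if it were the only primary outcome. With no lead score and no lead time, the protocol does not fix which comparison decides whether TTM worked.

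Two things are at stake. First, with many unranked primary comparisons each read at 0.05, the chance that at least one is significant by luck is several times 5%. Second, the 80% power applies to one score at one unspecified time. If the error rate over the whole primary family were later controlled, that power would no longer hold at the planned size.

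**Working it through.** **Counting the family.** Scores: SCL-90-R Global Symptom Index 1, MADRS-S 1, HADS 2, COPM 2, SDO 1, OBQ 1, total 8. Post-baseline times: 3. Upper limit 8 × 3 = 24 comparisons. Baseline comparisons are left out because they do not test a treatment effect.

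**The plan's own figure.** No SD is stated, so 60 per group cannot be checked independently. Solving for the SD with a two-sided test (sidedness is not stated; two-sided is assumed):

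SD = 3.6 / [(1.960 + 0.842) × √(2/60)] = 7.04, so d = 3.6/7.04 = 0.51.

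With the t distribution in place of the normal, d = 0.516. These values take the 60 as correct; they do not confirm it.

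**False-positive chance under independence, each test at 0.05 two-sided.**

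- 8 scores at one time: 1 − 0.95^8 = 0.337.
- 24 tests: 1 − 0.95^24 = 0.708.
- 24 tests, counting only results favouring TTM: 1 − 0.975^24 = 0.455.
- One score per instrument at three times: 1 − 0.95^18 = 0.603.

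**Under correlation.** The documents give no correlations, so these are assumed. Test statistics were simulated (400,000 draws) as normal variables with a common correlation between scores and a common correlation between times.

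| Between scores | Between times | Any false positive, 24 tests | Favouring TTM, 24 tests |
|---|---|---|---|
| 0.3 | 0.5 | 60% | 33% |
| 0.3 | 0.7 | 55% | 29% |
| 0.5 | 0.5 | 53% | 27% |
| 0.5 | 0.7 | 47% | 24% |
| 0.7 | 0.5 | 42% | 21% |
| 0.7 | 0.7 | 37% | 19% |
| 0.8 | 0.8 | 28% | 14% |

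For eight scores at a single time, the two-sided figures are 30%, 25% and 19% at between-score correlations of 0.3, 0.5 and 0.7.

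**Cost of controlling the whole family (Bonferroni, as an illustration).** Power ≈ Φ(d√(n/2) − z), with d√(n/2) = 0.5115 × √30 = 2.802.

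- 8 tests: alpha 0.05/8 = 0.00625, z = 2.734, Φ(0.067) = 0.527. The t-test with d = 0.516 gives 0.518.
- 24 tests: alpha 0.05/24 = 0.00208, z = 3.078, Φ(−0.277) = 0.391. The t-test gives 0.378.

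By the normal formula, restoring 80% power would need 98 or 118 per group, against 65 randomized.

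**The SDO scale.** Items are rated 1 to 7. Nine items summed give 9–63, the range in the power calculation. The Primary outcomes section says that this study uses a 14-item version, which summed the same way gives 14–98. The one powered outcome is therefore powered on a range that fits a different version.

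**The case against.** The strongest objection is that 24 tests and an any-one-counts rule are not in the document. The analysis section commits to comparing outcomes at the listed times with non-parametric methods. It does not promise one test per score per time, and it does not say that each HADS subscale or COPM rating is a separate endpoint. Nor does it say that one significant result would establish an effect of TTM. A decision rule or multiplicity procedure may sit in an analysis plan that is not shown. This stands as far as it goes: 24 is an upper limit, and the absence of an adjustment paragraph is not the point made here.

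A reader might also infer that a chance primary effect is likely. The documents do not support that. The two-sided figures include false results favouring the control group. Independence is implausible, since MADRS-S, HADS depression and the Global Symptom Index overlap in content. For false results favouring TTM the figure stays below one half throughout: 46% under independence and about 19–33% under the assumed correlations.

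The power figures rest on a back-solved effect size and a t-test, whereas the plan is non-parametric. Bonferroni is also a conservative way to control the error.

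What the objection does not remove is what the protocol itself fixes: an unranked primary list, no lead time, and a sample size built on one member of that list at the full 0.05. A later analysis plan could add an adjustment over the family, but the stated 80% power would then no longer apply.

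**Conclusion.** The point holds in this form: the protocol sets up an unranked primary family of six instruments (up to eight scores) at three times with no lead time, and sizes the trial for SDO alone at an undivided 0.05 and no stated time.

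If every score is tested at every time, the chance of at least one false-positive primary result is 71% under independence and about 37–60% with assumed correlations of 0.3–0.7 between scores and 0.5–0.7 over time. Counting only results favouring TTM, it is 46% and about 19–33%. These are several times the nominal error, but they do not make a spurious TTM effect the expected outcome. The size depends on correlations that the documents do not give, and on how many of the possible tests are in fact run.

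The power loss, from 80% to about 52% or 38% under Bonferroni, assumes two-sided testing and that the sponsor's 60 per group is right. Because this decides what would count as a positive trial, it should be settled before results are seen.

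**What to change.** Before unblinded data are seen:

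1. Name one primary score at one pre-specified time, tested at two-sided 0.05. SDO is the natural choice because the sample size is built on it. Nothing in the document favours the end of the intervention over 3 or 12 months, so the sponsor should choose the time and justify it.
2. Make the other scores and times secondary, either tested by Holm or in a fixed order, or reported as estimates with confidence intervals.
3. Align the primary objective, which now leads with symptoms and omits occupational balance.
4. If a symptom score must stay primary, fix one score and one time, use Holm across the two, and restate the power. At the first Holm step (alpha 0.025, z = 2.241), SDO power at 60 per group is about Φ(2.802 − 2.241) = 0.71.
5. When naming SDO, restate its power basis for the 14-item version, including the score range and the SD.

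The cost is wording in the protocol and analysis plan, with no new data; any registry entry that lists primary outcomes should be checked for consistency. The downside is that fewer results can be called primary. Inclusion began in January 2013, so this is a change to the primary outcomes of an ongoing trial. It should be dated and reported as such.
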